**Figure 2 F2:**
[figure not shown]
RECEIVER Study DesignACP, anticipatory care plan; CAT, chronic obstructive pulmonary disease assessment tool; COPD, chronic obstructive pulmonary disease; ED, emergency department; EHR, electronic health record; EMG, electromyography; FOT, forced oscillation technique; GOLD, Global Initiative for Chronic Obstructive Lung Disease; GP, general practitioner; HTA, Health Technology Assessment; ML, machine learning; MRC, Medical Research Council dyspnea scales; NHS, National Health Service; NHS GG&C, National Health Service Greater Glasgow & Clyde; NIV, non-invasive ventilation; PROs, patient-reported outcomes; QoL, quality of life; SMS, Short Message Service.

### Study population

People with high-risk COPD attending secondary care in the North and South Sectors of NHS GG&C will be screened for inclusion in this study.

Inclusion criteria:

Confirmed diagnosis of COPD, established prescreening or at screening, defined as per Global Initiative for Chronic Obstructive Lung Disease (GOLD) 2020 guidelines.^6^Home NIV cohort: hypercapnic respiratory failure and/or sleep disordered breathing, meeting established criteria for provision of home NIV.Exacerbation cohort: presentation within last 12 months with severe or life-threatening exacerbation of COPD, defined as per GOLD 2020 guidelines.^6^Participant or close contact who has daily access to smartphone, tablet or home computer with internet access.Informed consent.>18 years of age.

Exclusion criteria:

Inability to comprehend informed consent.Communication barrier precluding use of COPD digital service.

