## Study methods and analysis

### Study design

This study is a prospective observational cohort hybrid implementation and effectiveness study.^26^ It will be performed according to the UK Policy Framework for Health and Social Care Research (2020).^27^ The clinical intervention component is regarded as a phase IV adoption study. Data visualisation to facilitate guideline-based care, supported self-management and home NIV are evidence-based COPD interventions.

In this study, we will evaluate the adoption of digitally integrated remote management service innovations to support routine clinical care. Implementation of these will be evaluated and the digital innovations will be iterated to optimise them, based on user experience accrued during the study. We will acquire a consented dataset for trial endpoint analysis including exploratory machine learning-based predictive modelling. The machine learning analysis will also allow us to prioritise data inputs for follow-up study.

Secondary outcomes for the RECEIVER cohort will be compared with those from matched cohorts of patients acquired from the NHS GG&C SafeHaven dataset. Ethics approval is in place to access this large database of de-identified data, to establish a control cohort from a historical time series and a RECEIVER trial concurrent time series. These cohorts will be matched for demographics, COPD severity and hospital admission frequency with the RECEIVER cohort.

We will conduct a substudy of additional baseline and follow-up physiological measurements (oscillometry, parasternal electromyography (EMG), home pollution monitoring) in patients in whom it is feasible to obtain these during their hospital admission and/or hospital attendance alongside their routine clinical care.

Additionally, we will conduct a substudy of clinical users, with platform tracking analytics to measure clinician time spent on the platform, and user experience data. Clinical team members involved in the delivery of patient support using the digital service will be eligible for inclusion and appropriate consent will be sought. The qualitative components will be acquired through semistructured group or 1:1 interviews conducted by trained members of the research team. Thematic analysis will be performed. Anonymised transcripts will be coded, and themes generated from the codes. Themes will be discussed within the research team to reach agreement and add rigour.

An overview of the study design is provided in figure 2.

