### Sample size

Previous NHS GG&C studies,^10 21^ combined with internal audit data (showing that 80% of patients have direct or daily smartphone, tablet or web access), indicate that recruitment of 400 participants across a 12-month period is feasible, and likely to provide adequate data to conduct meaningful primary and secondary endpoint analyses.

An improvement in admission-free survival, with reduction in admissions by one per patient per year is projected, if support for provision of evidence-based COPD care is achieved by the service model. As the feasibility of an end-to-end digitalised service model for COPD has not yet been tested, and the service components will be adapted during the study, sample size power calculations and randomisation are not yet appropriate.

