## Statistics and data analysis

Secondary outcomes in the RECEIVER observational cohort will be compared with matched retrospective data from de-identified linked datasets of historical control and contemporary control high-risk patients with COPD. These will comprise of patients identified from coding and admission data as having had severe exacerbation of COPD between 1 January 2010 and 30 April 2019 (historical cohort) and between 1 July 2019 and 30 June 2020, excluding participants enrolled in the RECEIVER Study (contemporary control). The historical control dataset will contribute to machine learning models development. Secondary outcome analysis will be separately compared between the RECEIVER cohort, historical cohort and contemporary control cohort. This component of the study is also separately registered with dataset access approval from NHS GG&C SafeHaven LPAC.

The clinical endpoint data will be reported as a proportion and 95% CI for that outcome, calculated by Kaplan-Meier method. Demographic data will be presented as mean and SDs, or medians and IQRs as appropriate. Correlation, t-test, analysis of variance and effect size analyses will be used as appropriate for secondary endpoint analysis, comparing results of clinical endpoint and patient-centred outcomes with NIV therapy and supported self-management parameters.

Machine learning ensemble methods will be used to develop binary classification problems for patient risk. Precision, recall, accuracy and C-statistics of the receiver operating characteristic curve will be used to evaluate model performance.

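### The SafeHaven controls all have a coded severe exacerbation, but RECEIVER also enrols home NIV/CPAP patients without one, and the article sets no control index date to align with recruitment

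*Protocol article*

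**What the plan says.** **Who enters RECEIVER.** Study population lists two cohorts: "Home NIV cohort: hypercapnic respiratory failure and/or sleep disordered breathing, meeting established criteria for provision of home NIV" and "Exacerbation cohort: presentation within last 12 months with severe or life-threatening exacerbation of COPD". The Abstract and the Introduction join the two routes with and/or, so either is enough. The Abstract adds COPD with sleep apnoea overlap and CPAP users to the first route.

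**Who enters the control cohorts.** Statistics and data analysis defines the controls as "patients identified from coding and admission data as having had severe exacerbation of COPD between 1 January 2010 and 30 April 2019 (historical cohort"), and applies the same exacerbation criterion "between 1 July 2019 and 30 June 2020, excluding participants enrolled in the RECEIVER Study (contemporary control"). No second route is given.

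**Matching.** Study design says: "These cohorts will be matched for demographics, COPD severity and hospital admission frequency with the RECEIVER cohort".

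**Follow-up.** Under Subsequent assessments and Definition of end of trial, participants are observed for 12 months from recruitment. Screening and eligibility assessment expects most of them to be recruited during the index admission. No start of follow-up is given for controls. The bed-day endpoint in Table 1 names a preceding and a following 12 months but no date that separates them.

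**What is compared.** Table 1 sets clinical events, mortality, bed days and treatment uptake, including home NIV uptake, against both SafeHaven cohorts. Sample size states that "sample size power calculations and randomisation are not yet appropriate", and that a "reduction in admissions by one per patient per year is projected".

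**The concern.** An external control comparison can be read as a service effect only if both groups could have met the same entry rule and are followed from an equivalent moment. The first condition fails on the face of the text. The second is left open.

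A participant who enters on home NIV or CPAP, with no severe exacerbation in the past year, is compared with people selected because they had one. The article itself says that home NIV improves admission-free survival after a life-threatening exacerbation with persisting hypercapnia, and that NIV is already routine care. A different share of NIV users in the two groups is therefore a difference in case mix, not an effect of the digital service. Home NIV uptake is also one of the compared outcomes, so recruiting on an indication for NIV can raise it by the entry rule alone.

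On timing, a participant may be recruited up to 12 months after the qualifying event and must be alive to consent. If a control's year began at the exacerbation, it would include early readmissions and deaths that a late entrant has already passed. Admissions, mortality and the projected cost savings would all inherit that difference.

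**Working it through.** There is no power calculation or effect estimate to reproduce. The statement that "recruitment of 400 participants across a 12-month period is feasible" concerns recruitment only. The check is a comparison of the text, followed by illustrative arithmetic on assumed rates, before any matching.

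**1. Eligibility**

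| | RECEIVER | Both control cohorts |
|---|---|---|
| Severe exacerbation route | Yes, within 12 months | Yes, within a calendar window |
| Home NIV/CPAP route without recent severe exacerbation | Yes | No |
| Internet access, own or through a close contact | Required | Not required |
| Start of follow-up | Recruitment | Not stated |

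Matching selects from a pool. As every pool member has a coded severe exacerbation, no choice of factors can return a control without one.

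**2. Time zero, if controls were counted from the exacerbation**

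Assumed: 30% readmitted in the first 90 days, 15% in each later 90 days, no service effect.

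- Four 90-day periods from the exacerbation: 1 − 0.70 × 0.85³ = 57.0%.
- Four 90-day periods from month 3: 1 − 0.85⁴ = 47.8%.
- Difference if everyone enrolled at month 3: 57.0 − 47.8 = 9.2 points.
- If only a share *p* enrols then and the rest at the index event, the difference is *p* × 9.2:

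| *p* | Spurious difference |
|---|---|
| 20% | 1.8 points |
| 30% | 2.8 points |
| 50% | 4.6 points |

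As the article expects most recruitment at the index admission, *p* should be below 50%.

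**3. The same question in admissions per year**

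Assume a stable rate *b* of 1 to 2 per year, multiplied by *m* = 2 to 4 immediately after the event, with the excess halving every *h* = 1 to 3 months. With λ = ln 2 / *h*, the expected count over 12 months starting at month *t* is

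*b* × [1 + (*m* − 1) × (e^(−λ*t*) − e^(−λ(*t*+12))) / (12λ)].

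With 70% starting at *t* = 0 and 30% at *t* = 6, the spurious difference is 0.3 × (count at 0 − count at 6):

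- Smallest case (*b* = 1, *m* = 2, *h* = 1): 0.3 × 0.12 = 0.04.
- Largest case (*b* = 2, *m* = 4, *h* = 3): 0.3 × 1.52 = 0.46.

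The projected effect is 1 admission per patient per year.

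**4. NIV mix**

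Let a share *f* of participants be NIV-only, with an admission rate *r* times that of exacerbation patients, and let controls have 2 admissions per year (assumed). The spurious difference is 2 × *f* × (1 − *r*). For *f* = 10-40% and *r* = 0.3-1.0 it runs from 0 to 2 × 0.4 × 0.7 = 0.56 per year in RECEIVER's favour. For any *r* above 1 the sign reverses. The documents give neither *f* nor *r*.

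**The case against.** The strongest reply concerns timing. A reader might infer that controls enter at their exacerbation and that the cohorts therefore differ in time zero. The article does not say so. It gives calendar windows for the qualifying event and notes that the SafeHaven component is separately registered, so an index-date rule may exist there or in an analysis plan. A reader might also quote the full 9-point difference, but that needs every participant to enrol three months late, against the stated expectation. Both replies stand. The timing point is therefore conditional and its size is cut to match.

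It can also be said that controls are not defined by an exacerbation alone, because they are matched on three further factors. That is correct, and matching may reduce imbalance among exacerbation patients. Demographics may already include deprivation, which Table 1 groups with age and sex in its demographics endpoint, and admission frequency overlaps with prior bed days. Neither is pressed here. The matching does not repair the missing NIV-only counterparts.

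A reader might infer that the NIV mix flatters RECEIVER. The documents do not support a direction: the Introduction counts patients needing home NIV as high-risk in their own right, so including them could make RECEIVER look worse.

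Read literally, the screening text asks for all inclusion criteria to be met, which would require both routes at once. The and/or wording in the Abstract and Introduction shows that they are alternatives.

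Finally, Study limitations concedes bias in general terms, the aim is feasibility, and the primary endpoint has no control comparison. This limits how much depends on the point. It does not tell a reader of the secondary results that the two groups were selected by different rules.

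**Conclusion.** The eligibility mismatch is established from the text: controls have one entry route, participants have two, and matching within the control pool cannot bridge them. Neither NIV status nor time since exacerbation is a listed matching factor.

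The timing problem is established only in part. The article fixes no control index date that corresponds to recruitment. If controls are counted from the exacerbation, the bias favours RECEIVER. On the assumed 30% and 15% readmission risks it is about 2 to 3 percentage points with 20-30% enrolling three months late, and under 5 points if fewer than half do. On the alternative assumptions above (30% enrolling six months late) it is 0.04 to 0.46 admissions per year, against a projected effect of 1. None of these rates comes from the documents, and matching could change them.

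The size and direction of the NIV-mix bias are not determined. The primary utilisation endpoint is unaffected; the point concerns the secondary comparisons with SafeHaven and the cost savings derived from them.

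Controls are also not filtered on internet access. A reader might try to turn this into a percentage, but the documents give no outcome rate for people without access, and matching on admission frequency would absorb some of any difference. It is a residual limitation without a figure.

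**What to change.** In Statistics and data analysis:

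1. Limit the SafeHaven comparison of clinical outcomes to RECEIVER participants with a severe exacerbation in the 12 months before recruitment, whichever route they entered by.
2. Give each matched control an index date at the same number of days since its qualifying exacerbation as its participant had at recruitment, and require the control to be alive on that date. Count the days in the same way on both sides, and split the preceding and following 12 months for bed days at this date.
3. Add home NIV status at the index date, where it is available, and the Charlson index to the matching or to the adjustment. The Charlson index is already in the listed EHR extract; NIV status is not named there. NIV started after the index date remains an outcome.
4. Report NIV/CPAP participants without a recent severe exacerbation descriptively.
5. State that controls could not be selected on internet access, as a remaining limitation.

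If the separately registered SafeHaven component already sets an index-date rule, cite it and check it against item 2.

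The cost is mostly wording and programming on data already to be extracted. NIV/CPAP-only participants leave the control comparison, and the loss of precision depends on their number, which the article does not state. Recruitment, the service and the primary endpoint do not change.

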## Data collection

### Data collection by research team

#### EHR data

The following data will be obtained from EHRs held within NHS GG&C SafeHaven: demographic, coded diagnosis list, Charlson Comorbidity Index, Scottish Index of Multiple Deprivation quintile, medication history, laboratory results, lung function results, ED attendance, hospital admission, pulmonary rehabilitation attendance data from 1 January 2010 onwards. These data will be presented for evaluation in a study machine learning analysis platform.

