### Data from PROs

Participants (or their family or carer) will complete PRO questionnaires in the patient web portal. Daily SMS and/or email notifications are provided as a prompt to complete these. There is support information in the associated website to assist participants with any difficulties with the patient portal. Additional support will be provided by the clinical users if required.

Participants will complete symptom diary and COPD assessment tool (CAT) questionnaire daily. Medical Research Council dyspnea score (MRC) and healthcare episode questionnaires will be completed weekly. EQ-5D-5L generic quality of life questionnaire will be completed every 4 weeks. These questionnaires have been integrated to improve question flow and simplify the user experience. Questionnaire flow content is included in the online supplemental material 1.

10.1136/bmjresp-2021-000905.supp1Supplementary data

PRO data are presented unmodified, in a ‘user-friendly’ format (co-designed with clinical users), in the clinician dashboard. These unmodified data will inform and enhance clinical encounters and patient–clinician communication.

Pilot user experience research shows that the daily PRO questions can be completed in ~70 s, with weekly questions taking an additional 90 s, and monthly generic quality of life questions taking an additional 5 min.

Specific permission for use of CAT questionnaire within this e-health system has been obtained. The use of other PROs is covered by available open licensing.

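### Internet access, communication and consent filters apply only to RECEIVER participants and the stated matching does not address them, so the secondary clinical comparisons are open to selection bias

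*Protocol article*

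**What the plan says.** Under Study population, the protocol article sets entry filters that go beyond disease. Digital access is required: "Participant or close contact who has daily access to smartphone, tablet or home computer with internet access". Two exclusions follow: "Inability to comprehend informed consent" and "Communication barrier precluding use of COPD digital service". Informed consent is itself an inclusion criterion. Data from PROs relaxes the practical demand: "Participants (or their family or carer) will complete PRO questionnaires in the patient web portal".

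Statistics and data analysis defines both control cohorts from coding and admission data, as patients with a severe exacerbation between 1 January 2010 and 30 April 2019 (historical) or between 1 July 2019 and 30 June 2020 (contemporary). The second is formed by "excluding participants enrolled in the RECEIVER Study (contemporary control").

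Study design gives the matching: "These cohorts will be matched for demographics, COPD severity and hospital admission frequency with the RECEIVER cohort". EHR data lists, apart from the demographic item, "Charlson Comorbidity Index, Scottish Index of Multiple Deprivation quintile" among the SafeHaven fields to be extracted. Sample size reports internal audit data "showing that 80% of patients have direct or daily smartphone, tablet or web access". Study limitations admits a general risk of bias without naming this source of it.

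**The concern.** A matched comparison removes only the differences that the matching variables carry. Here one side has passed filters on connectivity, communication and willingness to take part, and the other has not. None of the three is a control criterion, a matching variable or a listed SafeHaven field. People without access or a supporting contact, or unable or unwilling to consent, may plausibly be more deprived, frailer or more isolated. If so, and if that extra risk is not captured by the matching variables, RECEIVER would look better than its controls even if the service did nothing.

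The contemporary cohort has a further difficulty. Taking enrolees out raises the share of people who could not or did not join.

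At stake are the comparisons with SafeHaven cohorts in Table 1: clinical events, mortality, bed days and treatment uptake. The projected savings from fewer admissions could inherit the same error. Sample size projects one fewer admission per patient per year, so a selection artefact could be taken as support for that projection.

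**Working it through.** **What can be reproduced.** The article gives no comparative effect, baseline rate or control size, and says that a power calculation is not yet appropriate. There is no stated result to reproduce. Only two usable inputs come from the document: the 80% access share and the target of 400 participants (both under Sample size). Everything else below is assumed and labelled so.

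**Access alone.** Let *a* be the access share among controls and *r* the residual rate ratio, no access versus access, after matching (assumed). Take access in RECEIVER as 100% and the service effect as nil. The apparent rate ratio, RECEIVER over control, is then

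RR = 1 / (a + (1 − a) r).

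For unselected controls, a = 0.80:

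- r = 1.0: 1 / 1.00 = 1.00
- r = 1.1: 1 / (0.80 + 0.22) = 1 / 1.02 = 0.98
- r = 1.25: 1 / (0.80 + 0.25) = 1 / 1.05 = 0.95
- r = 1.5: 1 / (0.80 + 0.30) = 1 / 1.10 = 0.91

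**Removing enrolees.** If all 400 came out of a contemporary pool of size P (assumed), the remaining access share would be a = (0.8P − 400) / (P − 400).

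| P (assumed) | a | RR at r = 1.1 | RR at r = 1.5 |
|---|---|---|---|
| 5000 | 3600/4600 = 0.78 | 0.98 | 0.90 |
| 2000 | 1200/1600 = 0.75 | 0.98 | 0.89 |
| 1000 | 400/600 = 0.67 | 0.97 | 0.86 |

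Depletion moves the ratio further from 1 whenever r exceeds 1. With a large pool it adds almost nothing.

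**Adding selection by consent.** Let *s* be the share of those with access who enrol, and *c* the residual risk ratio of connected non-enrolees to enrolees. Set the enrolee risk to 1, and assume s = 0.5, c = 1.1, r = 1.25.

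- Risk with access: 0.5 + 0.5 × 1.1 = 1.05. Risk without access: 1.25 × 1.05 = 1.3125.
- Historical: 0.8 × 1.05 + 0.2 × 1.3125 = 1.1025, so RR = 0.91.
- Contemporary: (0.8 × 0.5 × 1.1 + 0.2 × 1.3125) / (1 − 0.8 × 0.5) = 0.7025 / 0.6 = 1.171, so RR = 0.85.

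With r = c = 1, both ratios are 1.00.

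**If the access filter is weaker than 80% suggests.** The audit counts patients' own access, whereas the criterion also accepts a close contact's. If 90% would qualify (assumed), r = 1.5 gives 1 / (0.90 + 0.15) = 0.95.

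**Is deprivation already matched?** EHR data lists SIMD quintile as an item separate from demographic data. Table 1 has an endpoint on the impact of demographics and other factors, and its list puts area deprivation next to age and sex. The two places point different ways. Comorbidity is not in the matching set on any usual reading.

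**The case against.** The strongest defence is that only risk left after matching matters. Matching on earlier admissions and COPD severity bears directly on later admissions, so the residual ratio may be close to 1. That stands, and it is why the illustration starts at 1.0.

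Several further points also stand. Close-contact access and carer completion of questionnaires soften the filter. The home NIV entry route has no counterpart in the control definition and could push the comparison the other way. Bed days are measured over the preceding as well as the following 12 months, which reduces fixed differences between cohorts. The primary endpoint uses no control, and Study limitations disclaims definitive proof.

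A reader might infer that the contemporary control consists only of decliners and people who failed the criteria. The article does not support that. Screening covers the North and South Sectors, while controls come from the NHS GG&C SafeHaven dataset. The control window also opens in July 2019, before the September 2019 start. Eligible, connected people who were never approached therefore remain in the pool. Nor need all 400 enrolees have been in it: NIV entrants need no exacerbation, and others may have had theirs up to 12 months earlier.

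It may also be said that the exact matching list belongs in an unseen analysis plan or in the separately registered SafeHaven component. But the article itself states both the control definition and the matching set, and as stated they do not meet the problem. A general caveat about bias does not reduce it.

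**Conclusion.** The structural point holds: three filters act on one side only, the contemporary control has enrolees taken out, and the stated matching neither covers the filters nor names comorbidity. Bias in favour of RECEIVER is the more likely direction, and it would be larger against the contemporary control. That is a judgement, because the article reports no outcome by access or consent.

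A reader might infer that the entry criteria alone make every clinical endpoint favour RECEIVER. The documents do not support this. The illustrative range of 0.98 to 0.91 against unselected controls rests on 80% access and an assumed residual ratio of 1.1 to 1.5. The lower contemporary figures rest also on an assumed pool size or enrolment share.

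Because the comparisons are secondary and the study is about feasibility, this is a change that should be made rather than a flaw that undermines the trial.

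**What to change.** In Study design, name the Charlson Comorbidity Index and SIMD quintile explicitly among the matching variables for both control cohorts, or adjust for them in both comparisons. Both are already to be extracted.

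From the screening versus recruitment log described under Primary endpoint measures, report non-enrolment by reason: no access, communication barrier, unable to consent, declined. Alongside each control comparison, give a selection-only sensitivity analysis using the observed access share and a range of assumed residual rate ratios that includes 1.0. State that the comparative conclusion applies to digitally connected, consenting patients.

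The cost is analysis wording and a short table, with no new recruitment or data collection. The price is somewhat fewer close matches and a more cautious claim. Charlson and SIMD stand in only partly for access and consent, and the log says nothing about people never screened, so some selection will remain whatever is done.
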